#### Sample size

2.13.2

The sample size calculation is based on a systematic review and meta-analysis of controlled trials assessing extrinsic feedback on recovery and motor learning in individuals with brain injuries. The analysis found a significant Standardized Mean Difference of 0.76 with participants in identical motor training programs, differing only in feedback provision [16]. With 58 participants, we will attain a statistical power of 81.8 %. To account for potential dropouts, we plan to enroll 70 participants (35 in each group).

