### Randomization

2.6

Participants will be assigned to groups using matched pairs randomization with a 1:1 allocation ratio. Matching will be based on dichotomized ages (adolescents 15–19 years, young adults 20–25 years) and GMFCS-E&R classifications. Within each stratum, participants will be grouped into pairs. A computer-generated randomization sequence will assign the first participant in each pair to either group, with the second assigned to the alternate. [name] will enroll participants and extract age and GMFCS-E&R classifications to create pairs. A third-party allocator will conduct randomization to ensure allocation concealment, with the sequence securely stored and revealed only after statistical analysis is complete.

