### Outcomes

2.10

Baseline (T1) and outcome assessments (T2, T3) will be performed on weekdays within a week before intervention commencement (T1), within a week after the end of intervention (T2), and 24 weeks after intervention initiation (T3). Assessments will be conducted at approximately the same time of day for each participant to minimize intraday variability. The primary endpoint is T2. Please view the assessment timeline in Fig. 2.

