#### Superiority margin

2.13.1

The change in real-world daytime extremity movement over 72 h from baseline to follow-up (T2) and long-term follow-up (T3) determines the superiority margin, set at a 10 % increase for both upper and lower extremities.

Due to the wide variability in extremity movement among adolescents and young adults with CP at GMFCS-E&R levels I-V (upper: 5.6 %–54.4 %; lower: 1.3 % - 19.4 % of daytime) ([name], manuscript), percentage change was chosen over absolute change. Superiority is claimed if the lower bound of the 95 % confidence interval for the Music Motion Feedback group surpasses the 10 % margin. While no universal threshold for clinically meaningful improvement exists, this margin aligns with chronic stroke findings, where a change of 575–752 accelerometer counts is considered a meaningful improvement (15 %-20 %) [25].

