##### The primary outcome

2.13.3.1

A linear mixed-effects model (LMM) will analyze the percentage change in real-world targeted extremity movement from baseline (T1) to 12 weeks (T2) and 24 weeks (T3). The model will include fixed effects for Group (Music Motion Feedback vs. Control), Time (T1-T2, T1-T3), and their interaction (Group × Time), adjusted for baseline extremity movement time and sex. A random intercept for each participant will account for individual differences in baseline differences, and a random slope for Time will model variability in improvement rates. If residuals indicate non-normality, a logarithmic transformation will be performed.

Given the moderate sample size, the analysis will be conducted using restricted maximum likelihood estimation. A Holm-Bonferroni correction will be applied to adjust for multiple comparisons. A planned subgroup analysis will evaluate age group effects (adolescents vs. young adults).

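### The stated 81.8% power is for a test of zero between-group difference; it was not calculated for the plan's 10% margin rule

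*Protocol article*

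**What the plan says.** **Power.** Protocol article, Sample size (2.13.2): "The analysis found a significant Standardized Mean Difference of 0.76 with participants in identical motor training programs", differing only in feedback. Then "With 58 participants, we will attain a statistical power of 81.8" per cent, and to allow for dropout "we plan to enroll 70 participants (35 in each group"). The section gives no alpha, SD, margin, second time point or multiplicity adjustment.

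**Success rule.** Superiority margin (2.13.1) sets the margin at a 10% increase on the percentage-change scale. Superiority is claimed when the lower 95% confidence bound lies above that margin, and the bound is described as belonging to the feedback group. The section introduces the margin through the change to T2 and "long-term follow-up (T3) determines the superiority margin".

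**Time point.** Outcomes (2.10): "The primary endpoint is T2".

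**Analysis.** The primary outcome (2.13.3.1) fits a mixed model with Group, Time and their interaction, and states: "A Holm-Bonferroni correction will be applied to adjust for multiple comparisons". It does not name the comparisons in that family.

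**The concern.** Power belongs to a particular decision rule. Here the sample size is justified with a rule that excludes zero, while success is declared with a rule that must exclude 10%. A margin on the group difference is harder to meet than a zero null, so the planned power would be overstated, perhaps greatly.

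The wording of the rule raises a second problem. A bound on one arm's own change is not a comparison. Both arms receive individualized training, so both may improve, and a criterion met by the feedback arm alone could be satisfied without any effect of feedback. At stake are what the trial can claim if it succeeds and how well it was equipped to succeed.

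**Working it through.** **Inputs from the document.** SMD 0.76; 58 analysed, hence 29 per arm under "matched pairs randomization with a 1:1 allocation ratio"; 70 enrolled (35 per arm); margin 10 percentage points.

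**Assumptions.** Two-sided alpha of 5%, inferred from the 95% interval in the success rule. The document gives no SD of percentage change, so a range is shown.

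**1. Reproduce 81.8%.** Two-sample t-test, zero null, n = 29 per arm:
- noncentrality = 0.76 × √(29/2) = 2.894; df = 56; critical t = 2.003
- power = 81.2% (normal approximation 82.5%)

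The stated 81.8% lies between the two. Alternatives do not fit: a one-sided 5% t-test gives 88.8%, and a two-sided 2.5% t-test gives 72.2%. The stated figure is therefore that of one unadjusted 5% test against zero.

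**2. Margin on the between-group difference.** With true difference 0.76 × SD, the effective SMD is (0.76 × SD − 10)/SD = 0.76 − 10/SD.

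| Assumed SD (points) | True difference (points) | Effective SMD | Power, 29 per arm | Power, 35 per arm |
|---|---|---|---|---|
| 20 | 15.2 | 0.260 | 16% | 19% |
| 30 | 22.8 | 0.427 | 36% | 42% |
| 50 | 38.0 | 0.560 | 55% | 64% |
| 100 | 76.0 | 0.660 | 69% | 78% |

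Because 10/SD is positive, the effective SMD is below 0.76 for every finite SD. With 29 per arm, power is therefore always below the 81.2% of the zero-null test.

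**3. Margin on the feedback arm's own change.** One-sample t, n = 29, df = 28, noncentrality = (feedback-arm change − 10)/SD × √29. At an assumed SD of 20 the feedback effect is 0.76 × 20 = 15.2 points, added to the control-arm change:

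| Control change | Feedback-arm change | Noncentrality | Power |
|---|---|---|---|
| 0% | 15.2% | 1.400 | 27% |
| +5% | 20.2% | 2.746 | 76% |
| +10% | 25.2% | 4.093 | 98% |

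Power depends on a control-arm change that the document does not state.

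Now remove the feedback effect and let both arms improve by 20%: noncentrality = (20 − 10)/20 × √29 = 2.693, and the rule is met with probability 74%.

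**4. Holm, with a zero null.** If the family were T2 and T3, the first step would be at 2.5%, with 72% power at that step (29 per arm). Over the whole procedure, by simulation, T2 is declared significant 76–79% of the time when T3 has the same effect (correlation 0 to 0.9), and 73% if the T3 effect is half as large (correlation 0.5). If T2 is outside the family, Holm costs it nothing.

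**The case against.** The strongest objection concerns the tempting inference that the trial simply lacks 81.8% power. The document does not support that without a condition. The bound is attached to the feedback group, and on that literal reading power can exceed 81.8%, as step 3 shows. This stands. What can be said is that the figure was not calculated for the rule.

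A reader might also infer that success requires both T2 and T3. The Outcomes section names T2 as the primary endpoint, and the sentence that claims superiority names no time point. T3 appears only where the margin is introduced. That is a passage to reconcile, not an established two-time-point rule.

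Nor does the Holm sentence refute the power. Its family is undefined, a detail an article may leave to the analysis plan. The 72% is only the first-step power under one possible family. If all 70 were analysed, a two-sided 2.5% test would have 81.0% power.

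The margin powers rest on assumed SDs, so they illustrate a range and are not a measured shortfall. The direction does not depend on them.

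Finally, one might read the sentence that "this margin aligns with chronic stroke findings" of 15%–20% as a further mismatch. It has no bearing on power: a lower bound above 10% is compatible with an estimate of 15–20%.

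None of this reconciles the two sections. The article itself fixes both the power and the success rule, so this is not a detail left to a later analysis plan.

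**Conclusion.** The concern holds in this form: on neither reading of the margin was the stated power derived for the stated success rule.

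- **Between-group margin:** power with 29 per arm is below that of the zero-null test for any SD, at about 16% to 69% over assumed SDs of 20 to 100 points.
- **Feedback arm's own change:** power is undetermined and may be higher than stated, but meeting the rule would not show superiority over control.

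These results assume a two-sided 5% level and a true SMD of 0.76. They use simple t-tests, without credit for the covariate adjustment in the mixed model. The T3 and Holm points are secondary and conditional. Because the primary success criterion is affected, this should be settled before the analysis.

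**What to change.** State the confirmatory success rule as the between-group difference in percentage change at T2. Reconcile the mention of T3 in the Superiority margin section with T2 as the primary endpoint, and state whether the T2 test lies inside the Holm family. Then choose one of two routes:

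1. Test that difference against zero at two-sided 5%, outside the Holm family. Attach about 81% power (58 analysed) to that test, and keep 10% as a benchmark for interpreting the estimate and its interval.
2. Keep the 10% margin on the between-group difference and restate the power with an assumed, justified SD and the alpha that applies.

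Both routes are changes of wording with no added participants. The price of the second is a less favourable power figure. If the sponsor wanted 80% power against the margin, about 234, 88 or 52 per arm would be needed at SDs of 20, 30 or 50 points, against 35 planned. That is a reason to make the choice openly.

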#### Statistical methods

2.13.3

The distributions of continuous data will be assessed using Quantile-Quantile (Q-Q) plots, histograms, and the Shapiro-Wilk test. Normally distributed continuous data will be analyzed with parametric statistics. If normality is not met, a logarithmic transformation will be applied. Ordinal data will use non-parametric statistics. Categorical data will be presented as frequencies and percentages. An intention-to-treat analysis will include data from all trial participants.

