#### Secondary outcomes

2.10.2

The secondary outcomes will evaluate changes in capacity and function. Participants will be split based on goal-directed training for upper or lower extremities. The effects of upper-extremity training will be assessed using the Action Research Arm Test (ARAT) total score, isometric arm strength, and maximum grip strength. For lower-extremity assessment, the Gross Motor Function Measure-66 (GMFM-66), isometric leg strength, and the 6-min walk test will be applied. In addition, attendance and adherence will be monitored as process measures.

**ARAT** consists of 19 items across four dimensions: grasp, grip, pinch, and gross arm movement. Each item is rated on a 4-point ordinal scale ranging from normal performance to inability to perform any part of the test. The maximum total score is 57 points, with higher scores indicating greater functioning [21].

A hand dynamometer will determine the percentage change in **maximum hand grip strength** (Jamar Technologies, Horsham, PA, USA). Participants will squeeze the device maximally. After one practice trial, three measurements will be taken, with rest periods. The highest value will be recorded as the maximum grip strength.

**GMFM-66** is a 66-item observational assessment divided into five dimensions: Lying and rolling, sitting, crawling and kneeling, standing, walking, running, and jumping. Each performance is rated on a 4-point ordinal scale: Does not initiate task, Initiates task (<10 %), Partially completes task (10–99 %), and Completes task (100 %). Calculations of GMFM-66 scores require the use of a computer program, Gross Motor Ability Estimator-3 (GMAE-3) [22].

**6MWT** measures submaximal aerobic and functional gait capacity. Able participants will walk 6 min on a 30-m walkway with the enclosed corridor length marked at every 3-m interval. Cones mark turnaround points. The total distance walked over the 6 min is used as the score [23].

**Isometric strength** will be assessed using handheld dynamometry by measuring maximal isometric force for muscle groups. Three measurements will be recorded with rest periods, and the highest value (kilogram force) per muscle group will be recorded as the maximum.

The TIA app will collect **attendance and adherence data**, which includes daily logins, session duration, and the time spent moving the targeted extremity.

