##### Secondary outcomes

2.13.3.2

Attendance (number of training sessions) and adherence (active practice time) will each be categorized based on the prescribed dose achieved: low (<33 %), medium (33–66 %), and high (>66 %). Chi-square tests will compare the two groups' attendance distribution and adherence levels.

The analysis of other secondary outcomes will follow the same approach as the primary outcome, using LMM.

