## Discussion

3

Music Motion Feedback is a promising approach to improving movement behavior and functional improvement in adolescents and young adults with CP, potentially increasing activity and reducing disability. By providing real-time extrinsic feedback in tailored home-based training, we utilize established motor learning principles to enhance adherence and long-term outcomes. However, the THRIVE-CP trial faces generalizability limitations, such as recruiting intrinsically motivated participants and the bias of CP severity affecting participation, with 70 % of participants projected at GMFCS-E&R I-II. Additionally, those with lower technological literacy may struggle with adherence to the Music Motion Feedback. The trial lacks a usual care group due to recruitment constraints, limiting our ability to assess the separate effect of Music Motion Feedback. However, the TRIVE-CP trial addresses a critical challenge faced by adolescents and young adults with CP. If effective, this technology could provide an accessible and scalable method to enhance adherence to home-based motor training and foster meaningful progress in real-world movement behavior and functional abilities. The findings may significantly impact practice by promoting sustainable behavioral changes and improving the quality of life for individuals with CP.

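### The plan gives two unreconciled triggers for a log transformation of the secondary outcomes, and under either one the automatic log is a poor remedy for the bounded scores (ARAT, GMFM-66)

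*Protocol article*

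**What the plan says.** Four statements in the protocol article bear on the scale of the secondary outcomes.

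- Section 2.13.3 (general rule): "The distributions of continuous data will be assessed using Quantile-Quantile (Q-Q) plots, histograms, and the Shapiro-Wilk test". It continues: "If normality is not met, a logarithmic transformation will be applied". It mentions neither residuals nor the direction of skew.
- Section 2.13.3, next rule: "Ordinal data will use non-parametric statistics".
- Section 2.13.3.1 (primary outcome): "If residuals indicate non-normality, a logarithmic transformation will be performed". The trigger differs; the remedy is the same.
- Section 2.13.3.2 (secondary outcomes other than attendance and adherence): "The analysis of other secondary outcomes will follow the same approach as the primary outcome, using LMM".

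On the scores themselves, section 2.10.2 says of ARAT "The maximum total score is 57 points, with higher scores indicating greater functioning" and of the GMFM-66 items "Each performance is rated on a 4-point ordinal scale: Does not initiate task". Section 2.3 admits GMFCS-E&R levels I to V, and the Discussion expects a sample "with 70 % of participants projected at GMFCS-E&R I-II". Section 2.10.2 also splits participants by targeted limb, so each score is analysed in a subset whose size is not given.

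**The concern.** A mixed model needs roughly normal residuals, not normally distributed outcomes. A sample that spans five severity levels can have a clearly non-normal outcome distribution and sound residuals, because baseline adjustment removes most of the spread between levels. The two triggers can therefore disagree, and the protocol does not say which one applies to the secondary outcomes.

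The remedy is a separate problem. A log pulls in a long right tail. With most participants at the mild end, a bounded score such as ARAT or GMFM-66 is more likely to have a long left tail, which a log stretches. The log also turns a difference in points into a ratio, a change of estimand made after the data are seen, and it cannot be computed for zero or negative values. At stake are the functional and limb-function hypotheses in section 1.1, which are tested in limb-specific subsets.

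**Working it through.** **1. The plan's own figure.** Section 2.13.2 gives 81.8 % power for 58 participants at a standardized mean difference of 0.76. With 29 per arm and two-sided 0.05 (assumed, since alpha is not stated there), the normal approximation is Φ(0.76 × √(29/2) − 1.96) = Φ(2.894 − 1.96) = Φ(0.934) = 82.5 %. The noncentral t gives 81.2 %. The figure is reproduced closely enough to use 0.76 as the effect size below.

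**2. Can ARAT be 0?** It has 19 four-category items and a maximum of 57. Since 57/19 = 3, items run from 0 to 3 and the minimum is 0. Section 2.3 sets no minimum arm or hand function. The log of 0 is undefined.

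**3. Direction of the log.** Take assumed level means of 88, 72, 57, 43 and 27 on a 0-100 scale. The top gap (88 − 72) and the bottom gap (43 − 27) are both 16 points. On the log scale they are ln(88/72) = 0.201 and ln(43/27) = 0.465, so the lower gap becomes 2.3 times the upper one. The left tail is stretched.

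**4. Do the triggers disagree?** Simulation, with follow-up score regressed on arm and baseline as a stand-in for the mixed model. All distributional inputs are assumptions except the 70 % at levels I-II and the 0.76.

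- *Set A*: 0-100 score, level means 88/75/55/40/22, within-level SD 6, residual SD 4, arm difference 3.6.
- *Set B, GMFM-like*: level split 40/30/13/10/7 %, means as in step 3, within-level SDs 6/7/6/6/7, residual SD 4, arm difference 0.76 × 4 = 3.04.
- *Set B, ARAT-like*: 0-57 score, same level split, means 50/45/35/22/10, with the within-level spread also assumed.

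| Setting | Outcome level fails Shapiro-Wilk | Residuals fail | Power without log | Power with log |
|---|---|---|---|---|
| A, n = 30 | 78.8 % | 5.0 % | 64.8 % | 56.0 % |
| A, n = 40 | 90.8 % | 4.5 % | 79.0 % | 67.5 % |
| A, n = 50 | 96.3 % | 5.3 % | 88.0 % | 77.6 % |
| B GMFM-like, n = 58 | 97 % | 5.6 % | 80 % | 72 % |
| B GMFM-like, n = 29 | 62-64 % | about 5 % | 45-47 % | 42 % |
| B ARAT-like, n = 58 | 100 % | 6 % | 73 % | 53 % |
| B ARAT-like, n = 29 | 98 % | 6 % | 42 % | 31 % |

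In set A the last column logs every trial; in set B it logs only trials where the outcome level fails the test. In set B at n = 58, skewness moves from −0.74 to −1.50 (GMFM-like) and from −1.17 to −2.40 (ARAT-like). Logging raises the share of trials with non-normal residuals from about 5 % to 39 % and from 6 % to 81 %.

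**5. Less favourable inputs.**

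- Set A with levels closer together (80/70/60/50/40, SD 9): 21 % of trials fail, and the power loss is about 3 points.
- Set B, GMFM-like, with effect and error proportional to baseline: 76 % without the log against 79 % under the distribution rule (n = 58), and 46 % against 48 % (n = 29). There is no loss.
- No true effect (GMFM-like, n = 58): type I error 4.8 % against 5.2 %.

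**6. If change is modelled.** With a mean gain of 2 points and residual SD 4, the share of changes at or below zero is Φ(−2/4) = 31 % in controls and Φ(−(2 + 3.04)/4) = Φ(−1.26) = 10 % in the feedback arm, or about 21 % overall. With proportional effects the simulated share is about 26 %. None of these values can be logged without an offset, whichever trigger is used.

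**The case against.** The strongest reply is that specific text governs general text. Section 2.13.3.2 sends the secondary outcomes to the primary approach, whose trigger is residual-based, and section 2.13.3 never says that raw scores are meant. A reader might infer that the plan definitely tests raw scores and logs them although the residuals are sound. The documents do not support that. They support only two differing triggers with no stated precedence.

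Second, the primary approach models change, and the simulated rejection rates concern outcome levels. This stands. On absolute change, Shapiro-Wilk rejects in only about 4 to 5 % of simulated trials; on percentage change, in about 50 to 67 %. The high rates in the table apply only if levels are tested. On a change scale the problem becomes the undefined log.

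Third, left skew is inferred from the ARAT maximum and the projected severity mix; no data are shown. The inference is reasonable for ARAT and GMFM-66. It does not extend to grip strength, isometric strength or the 6-minute walk, which have no stated upper limit; the walk is also limited to participants able to do it.

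Fourth, a reader might infer that ARAT and GMFM-66 are sent both to a non-parametric test and to a mixed model. Section 2.13.3.2 assigns them to the mixed model and section 2.13.3.3 assigns COPM to Mann-Whitney, so the routing is largely settled and needs only a clarifying clause.

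The unseen statistical analysis plan may refine this. The protocol nevertheless states the rules itself, and they differ.

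**Conclusion.** The point holds in a limited form and concerns the secondary outcomes only. Two parts need no simulation: sections 2.13.3 and 2.13.3.1 give different triggers that section 2.13.3.2 does not reconcile, and the sole remedy is undefined for an ARAT of 0 and for zero or negative changes. That the log worsens the fit of ARAT and GMFM-66 rests on the inferred left skew.

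A reader might infer a sure loss of power. That is not supported. The loss is about 3 to 20 points under additive effects, depending on score, subset size and assumed spread of levels. The 20-point figure is for the ARAT-like score at n = 58, and a subset that large is unlikely if both limbs are well represented. The loss vanishes when effects scale with baseline. Type I error is not affected. The change is worth making because the rule can alter scale and estimand after the data are seen, and correcting it is cheap.

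**What to change.** - In section 2.13.3, limit the distribution check to descriptive use.
- State one rule for all secondary outcomes analysed by mixed model: assumptions are judged from residual plots.
- Keep ARAT and GMFM-66 on their original scale. If residuals are clearly non-normal, retain scale and estimand and use bootstrap or robust confidence intervals in place of the automatic log.
- Say that the sentence on ordinal data refers to COPM, as sections 2.13.3.2 and 2.13.3.3 already imply.

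This takes a few sentences in the protocol, repeated in the statistical analysis plan. The downside is that bootstrap or robust intervals may be slightly wider. Other remedies that keep the scale would also serve; what matters is that one is fixed in advance.
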